## Abstract

**Background:**

Acute kidney injury (AKI) is associated with poor outcome in critically ill children. While data extracted from retrospective study of pediatric populations demonstrate a high incidence of AKI, the literature lacks focused and comprehensive multicenter studies describing AKI risk factors, epidemiology, and outcome. Additionally, very few pediatric studies have examined novel urinary biomarkers outside of the cardiopulmonary bypass population.

**Methods/Design:**

This is a prospective observational study. We anticipate collecting data on over 5000 critically ill children admitted to 31 pediatric intensive care units (PICUs) across the world during the calendar year of 2014. Data will be collected for seven days on all children older than 90 days and younger than 25 years without baseline stage 5 chronic kidney disease, chronic renal replacement therapy, and outside of 90 days of a kidney transplant or from surgical correction of congenital heart disease. Data to be collected includes demographic information, admission diagnoses and co-morbidities, and details on fluid and vasoactive resuscitation used. The renal angina index will be calculated integrating risk factors and early changes in serum creatinine and fluid overload. On days 2–7, all hemodynamic and pertinent laboratory values will be captured focusing on AKI pertinent values. Daily calculated values will include % fluid overload, fluid corrected creatinine, and KDIGO AKI stage. Urine will be captured twice daily for biomarker analysis on Days 0–3 of admission. Biomarkers to be measured include neutrophil gelatinase lipocalin (NGAL), kidney injury molecule-1 (KIM-1), liver-type fatty acid binding protein (l-FABP), and interleukin-18 (IL-18). The primary outcome to be quantified is incidence rate of severe AKI on Day 3 (Day 3 – AKI). Prediction of Day 3 – AKI by the RAI and after incorporation of biomarkers with RAI will be analyzed.

**Discussion:**

The Assessment of Worldwide Acute Kidney Injury, Renal Angina and Epidemiology (AWARE) study, creates the first prospective international pediatric all cause AKI data warehouse and biologic sample repository, providing a broad and invaluable resource for critical care nephrologists seeking to study risk factors, prediction, identification, and treatment options for a disease syndrome with high associated morbidity affecting a significant proportion of hospitalized children.

**Trial registration:**

ClinicalTrials.gov: NCT01987921

**Electronic supplementary material:**

The online version of this article (doi:10.1186/s12882-015-0016-6) contains supplementary material, which is available to authorized users.

## Background

Acute kidney injury (AKI) is associated with poor outcome in critically ill children. The reported incidence rate of AKI in children admitted to pediatric intensive care units (PICUs) range from 8% and 89% [1-6]. AKI has been associated with prolonged hospital stay, progression to chronic kidney disease, and a significantly higher relative risk of in-hospital death [7-10]. The epidemiology and outcomes of adult AKI have been validated through large, multi-center studies describing over 20,000 adult patients [11-13]. Unfortunately, the current pediatric literature lacks such extensive studies. To date, the largest study about AKI in children admitted to PICU was carried by Schneider et al. on 3396 children [1]. Despite the large population size, this was a single-center study and also did not use the pediatric RIFLE criteria to define AKI, the standard for pediatric AKI definition before the recent KDIGO consensus criteria [4,14]. Aside from a few single center studies, most knowledge of pediatric AKI is gleaned from retrospective studies with relatively small sample sizes and with diverse AKI definitions [2,4,15]. To date, there is no multicenter prospective study describing the epidemiology and outcome of pediatric AKI in PICUs.

Despite increasing awareness of the prevalence and significance of AKI, effective therapies for this condition are lacking. This, at least in part, stems from a failure to recognize AKI before a significant degree of renal damage has already occurred. The inability to diagnose AKI expeditiously follows from the fact that the currently accepted definitions of AKI rely on changes in serum creatinine (SCr) and urine output [4]. The well-recognized limitations of SCr have been previously described [16,17]. Intensive basic and translational research has targeted the discovery of biomarkers able to uncover AKI prior to elevations in serum creatinine. To date, a number of promising candidate urinary AKI biomarkers have emerged following preliminary proteomic analyses in murine models of renal ischemia [18]. Clinical studies indicate that urinary neutrophil gelatinase-associated lipocalin (NGAL), kidney injury molecule-1 (KIM-1), interleukin 18 (IL-18) and liver-type fatty acid binding protein (L-FABP) all predict AKI in children following cardiopulmonary bypass prior to changes in serum creatinine [19-21]. Widespread clinical extrapolation of these results is challenging, however, given their derivation and validation in homogenous populations free from common co-morbidities and exposed to a uniform insult on a known time scale. New adult-specific data indicate that plasma NGAL demonstrates reasonable predictive performance in heterogeneous patients, with variable comorbidities, presenting to the emergency room [22]. Neither plasma NGAL, nor the other biomarkers listed above, have demonstrated robust efficacy in children with heterogeneous illness when tested in isolation. Additionally, select early papers utilized definitions of AKI that may have contributed to the high sensitivities subsequently achieved by urinary biomarkers [23]. Such issues may underlie these urinary biomarkers' inability to predict AKI severity, identify children who would require renal replacement therapy (RRT), and predict AKI-associated death [23-27]. In response to a need of clinical predictors of AKI, we proposed the renal angina clinical model [28,29]. In this model, a composite of clinical risk factors and clinical evidence (the renal angina index (RAI)) of acute kidney injury directs biomarker testing, akin to directed assessment of troponin I only in select patients with chest pain. This model seeks a high negative predictive value (NPV) for AKI of *not fulfilling renal angina*. Further, unlike difficult to use, severity of illness scoring systems which merely score existing injury, fulfillment of renal angina aids *prediction* of severe AKI. In relatively small, retrospective studies, we have demonstrated that the RAI offers moderate discrimination for severe AKI, prediction which improves after the incorporation of biomarkers [30]. This ‘targeting’ of biomarker testing demonstrates a methodology to optimize the utility of novel diagnostics.

Given the paucity of prospective studies directly aimed at investigating pediatric AKI in critical illness, a large and diverse observational study is needed to enrich the field of pediatric critical care nephrology with current data. In this manuscript we describe the methodology of the Assessment of Worldwide AKI, Renal Angina and Epidemiology (AWARE) study. The AWARE repository will facilitate analysis of epidemiologic trends, refine risk stratification, solidify associated morbidities, identify disparities across the globe, and potentially uncover information vital to mitigating the burden of the AKI syndrome.

## Methods/Design

### Design

The design is a prospective, multi-center, observational trial of critically ill children admitted to the pediatric intensive care unit (PICU).

### Setting

The setting is 32 PICUs across 5 continents and 12 countries. Site investigators are listed in Additional file 1.

### Population

Eligible participants fulfill all inclusion and no exclusion criteria.

### Inclusion criteria

The inclusion criteria are designed to capture as many potential study patients as possible and are inclusive of most patients admitted to the PICU and cardiac intensive care unit (CICU). All inclusion criteria must be met and only patients with an ICU length of stay of at least 48 hours are included in data analysis (other patient data is kept for demographic data repository, but excluded from data analysis for renal angina or AKI associated outcome).In-patient in a PICU or CICUAge ≥ 90 daysAge < 25 years

### Exclusion criteria

Maintenance hemodyialysis or peritoneal dialysis.Chronic kidney disease with a baseline estimated glomerular filtration rate (eGFR) of < 15 ml/min/1.73 m^2^.Kidney transplant within 90 days of PICU/CICU admission.Post-operative from surgical correction of cyanotic congenital heart disease within 90 days of PICU/CICU admission.Uncorrected congenital heart disease (does NOT include patients with an isolated atrial or ventricular septal defect, patent ductus arteriosus, or patent foramen ovale).Immediately following elective cardiac catheterization.

For exclusion criteria 4–6, patients admitted and then taken to the operating theater for surgical corrections requiring cardiopulmonary bypass are included for study.

### Urine collection

For sites that have agreed to collect urine samples, eligible patients for study will have urine collected from an indwelling urinary catheter (foley) or via clean intermittent catheterization twice daily (between 6 and 10 am and between 3 and 7 pm) within the first 48 hours of admission (and then for as many of the regularly scheduled samples as possible within the first 4 days of PICU/CICU admission). Patients are not bagged or catheterized separately/independently for the purposes of this study. Collected urine samples are kept on ice or in 4°C refrigerator until they are processed. During processing, specimens are centrifuged at 3000 RPM at 4°C for fifteen minutes. The supernatants are divided into up to nine 1-mL cryovials depending on the collected urine volume and stored at minus 80°C. The stored urine samples from all participating sites are shipped to the Center for Acute Care Nephrology/Nephrology Center of Excellence Biomarker Core Laboratory in the Division of Nephrology and Hypertension at Cincinnati Children’s Hospital Medical Center.

### Urinary biomarker sampling

Urine NGAL will be assayed using a human-specific commercially available enzyme-linked immunosorbent assay (ELISA, AntibodyShop, Grusbakken, Denmark). Urine IL-18 and L-FABP will be measured using commercially available ELISA kits (Medical & Biological Laboratories Co., Nagoya, Japan, and CMIC Co., Tokyo, Japan, respectively) per manufacturer’s instructions. Urine KIM-1 is measured by ELISA using commercially available reagents (R&D Systems, Inc., Minneapolis, Minnesota).

### Variable collection

Data collected per patient encompasses admission demographic data, daily morning hemodynamic parameters, daily laboratory values specific for kidney function, assessments of fluid balance including net fluid in and net fluid out, and use of nephrotoxins or diuretic agents. For admission epidemiology, primary ICU diagnoses are broadly divided into shock/infection/major trauma, medical cardiac, respiratory failure, post-surgical/minor trauma, central nervous system dysfunction, and pain/sedation management. Net fluid balance is divided into total fluids and urine flow rates derived per kilogram admission body weight per hour. Daily calculated values include:Estimated change in creatinine clearanceCalculated as percent change of daily creatinine from baseline creatinine.Baseline creatinine used is lowest consistent serum creatinine 90 days or more prior to admission.For patients without a prior baseline, an assumed creatinine clearance of 120 ml/min/1.73 m^2^ is used [3].Percent fluid overloadCalculated as previously described [31].Fluid corrected serum creatinineCalculated as previously described [32].KDIGO stage AKI by creatinineBased on KDIGO AKI guidelines [33].

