### Primary and secondary outcomes

Our primary outcome is to report the epidemiology and associated outcomes of pediatric AKI worldwide (in over 30 PICUs, 12 different countries, 5 continents). This outcome is dependent on broad enrollment from participating centers. AKI is defined as KDIGO stage 2 or 3 AKI by creatinine and/or urine output criteria on Day 3 or later of PICU/CICU admission (Day 3 AKI).

Our secondary outcomes are to validate and refine the renal angina risk stratification model for prediction of Day 3 AKI.Determine if fulfillment of renal angina on Day 0 is predictive of severe AKI on Day 3 of PICU/CICU admission across the heterogeneous patient landscape of our participating centers. The AWARE data repository will be used to validate the precision of the RAI in ruling out AKI.Determine if prediction of Day 3 AKI by an RAI ≥ 8 is augmented by inclusion of urinary biomarkers alone or in combination.

Longer term outcomes to be followed include duration of mechanical ventilation, use of continuous renal replacement therapy, use of extracorporeal assist devices such as extracorporeal membrane oxygenation (ECMO) or ventricular assist devices (VADs), ICU length of stay, and mortality (Day 30 follow up).

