The design of this prospective study has limitations. We make several assumptions with regards to the expected incidence of AKI per PICU/CICU center. Differing geographic areas included in our enrollment study list and different patient demographics may have greater or less incidence of AKI risk. Many pediatric patients have no ‘baseline’ creatinine measured prior to the time of acute illness. Our assumption of a normal creatinine clearance is based on the use of this paradigm in previous study [4]. Additionally, we assume that 33% or greater of our enrollment sites will be able to capture urine for the biomarker analysis. Perhaps the greatest limitation is that this study is being independent of financial reimbursement. Study coordinators, research coordinators, and data management specialists at each site are not compensated for the exclusive purpose of this study, which has the potential to bias the enrollment strength of each center (depending on staff enthusiasm and availability). All of these limitations can also be interpreted as strengths of the study, however. Our initial results indicate that the AWARE study will assemble a broad and heterogeneous patient repository and that the pro bono work done by our coordinating sites is robust. It is our expectation that the AWARE study will serve as a model, a proof of concept that resources are in place to facilitate broad based pediatric AKI studies, for future large scale multicenter studies that are funded and sponsored by governmental and private financial support.

AKI is a significant disease syndrome affecting a large proportion of pediatric ICU patients. Existing data indicates that patients are not just dying with AKI, but *from* AKI [35]. AWARE is a first of its kind and vital study of critically ill children that will inform the pediatric critical care nephrology community of the prevalence and associations of AKI across the globe, offering new perspectives for prediction and detection of disease.

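### The baseline creatinine window bars every value from the 90 days before admission, although children enter from age 90 days; this pushes more of them onto an assumed clearance and can misstate AKI stage

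*Protocol article*

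**What the plan says.** All places are in the protocol article.

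- **Variable collection**, measured baseline: "Baseline creatinine used is lowest consistent serum creatinine 90 days or more prior to admission". No upper limit is set on how old the value may be, and no other section gives a different window.
- **Variable collection**, fallback: "For patients without a prior baseline, an assumed creatinine clearance of 120 ml/min/1.73 m^2^ is used".
- **Variable collection**, a daily item labelled as a change in clearance is computed as "percent change of daily creatinine from baseline creatinine". KDIGO stage by creatinine is listed as a separate daily value.
- **Inclusion criteria**: entry from age 90 days to under 25 years. **Exclusion criteria**: chronic kidney disease is excluded only below an eGFR of 15, or on maintenance dialysis.
- **Primary and secondary outcomes**: "AKI is defined as KDIGO stage 2 or 3 AKI by creatinine and/or urine output criteria on Day 3 or later".
- **Abstract, Methods/Design**: "The renal angina index will be calculated integrating risk factors and early changes in serum creatinine and fluid overload". The full RAI definition is in Additional file 2, which is not shown.
- **Discussion**, limitations: "Many pediatric patients have no ‘baseline’ creatinine measured prior to the time of acute illness".

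**The concern.** A baseline should describe the child's kidney function shortly before the present illness. This rule discards the values most likely to do that and keeps older ones without limit, in a population where creatinine changes with growth. It also sits badly with an entry age equal to the length of the barred period.

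The Discussion attributes missing baselines to children never having been measured before they fell ill. The window adds a second group: children who were measured before the illness, but too recently. They are treated as having normal function.

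Creatinine-based staging feeds the primary outcome. If the Day 0 RAI takes its creatinine change from the same baseline, one error enters both predictor and outcome, and the accuracy measures in the Analysis section could look better than they are.

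**Working it through.** The article states no figure on this point, so there is nothing to reproduce first.

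**Step 1: what the window leaves.** Inputs: minimum age 90 days (Inclusion criteria); minimum age of the baseline value 90 days (Variable collection). Latest permitted age at sampling = age at admission − 90.

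| Age at admission (days) | Latest permitted sample (day of life) | Share of life usable |
|---|---|---|
| 90 | 0 | 0% |
| 120 | 30 | 25% |
| 150 | 60 | 40% |
| 180 | 90 | 50% |
| 365 | 275 | 75% |

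The window is empty in practice at the entry limit and confined to early infancy up to about six months. For older children it is not empty, but recent values remain barred.

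**Step 2: what the fallback does to such a child.** Assumption, not in the article: clearance is inversely proportional to creatinine at constant body size. A child with stable true clearance C and no acute change then shows an apparent creatinine ratio of 120/C:

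- C = 80: 120/80 = 1.5
- C = 60: 120/60 = 2.0
- C = 40: 120/40 = 3.0

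All three children are eligible, because exclusion starts below 15. A recent stable creatinine would have given a ratio of 1.0.

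**Step 3: what an over-old value does.** Illustrative values: creatinine just before the illness 0.3, today 0.6, so the ratio is 0.6/0.3 = 2.0. An older value of 0.2 gives 3.0; one of 0.4 gives 1.5. The error can run either way.

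**Step 4: shared error, if the RAI uses the same baseline.** I simulated 400,000 children. Every input here is an assumption.

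- Observed ratio = (120/C) × change; C is normal with mean 105, kept above 15.
- Log change has mean 0.05 and SD 0.25, drawn independently for Day 0 and Day 3.
- Outcome: Day 3 ratio of at least 2. Predictor: Day 0 ratio. Every child is given the assumed 120.

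| SD of true baseline | Apparent doubling on Day 3 | AUC of Day 0 ratio |
|---|---|---|
| 10 | 3.0% | 0.59 |
| 15 | 4.4% | 0.68 |
| 20 | 6.6% | 0.76 |
| 25 | about 9% | 0.82 |

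With the true baseline, doubling is 0.5% and the AUC about 0.50. Moving the mean to 90 or 120 at SD 25 barely changes the AUC (0.82 and 0.83), so the SD drives it. The mean does move the apparent rate: mean 120 with SD 15 gives 1.3%. With only 30% of children on the assumed baseline (mean 105, SD 25), the AUC is 0.83 and apparent doubling about 3%.

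Now let acute changes persist: log-change correlation 0.6 between Day 0 and Day 3, change SD 0.35. The AUC is 0.86 with the true baseline. With the assumed baseline it is 0.86 at SD 15 and 0.89 at SD 25.

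**Step 5: the clearance label.** With r = daily/baseline creatinine, the stated formula gives r − 1, whereas a change in clearance would be 1/r − 1 under the Step 2 assumption. For r = 2 these are +100% and −50%. The label and the formula describe different quantities.

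**The case against.** - **The assumed clearance is cited and openly declared.** The Discussion lists it as a limitation. That stands for children with no earlier creatinine. It does not cover children who have one that the window excludes.
- **The simulation tests the assumed clearance, not the window.** This stands. The window harms children who have a value from the last 90 days and none older, or whose older value is out of date. The article gives neither share.
- **Independent Day 0 and Day 3 changes are artificial.** This stands too. A reader might infer from 0.50 against 0.82 that the planned RAI accuracy would be largely spurious. The documents do not support that: the SD of 25 is not theirs, real injury persists over days, the outcome also uses urine output, the RAI also uses risk factors and fluid overload, and its definition is not shown.
- **Young infants still get a baseline.** A reader might infer that the rule is unusable in all young infants. It is effectively empty only near 90 days of age, a 150-day-old has a 60-day window, and the fallback always assigns something.
- **The clearance item could be read as corrupting the endpoint.** It does not. KDIGO stage is calculated separately, and no analysis in the Analysis section names the clearance item. How 120 is turned into a creatinine may properly be left to the cited source or the full protocol.
- **The wording may be a slip for a window within 90 days.** That is possible, but nothing in the article shows it. Sites entering data on common forms need one clear rule.

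**Conclusion.** The concern holds for the baseline window. As written, the rule excludes recent pre-illness creatinine, does not fit an entry age of 90 days, and sends additional children to an assumed normal clearance. The arithmetic in Step 1 needs only the article's own figures. That creatinine-based staging can be misstated rests on one further reading: that staging uses the only baseline the article defines.

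Inflated RAI accuracy is possible, not shown. It is conditional on the RAI using the same baseline. Its size runs from little or none (0.86 against 0.86 to 0.89 with persistent kidney changes) to an AUC of 0.59 to 0.82 where no association exists, over SDs of 10 to 25 with every child on the assumed baseline. The documents give neither the spread of true baselines nor the share of children affected, so no single figure should be quoted.

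The clearance item is a naming error of minor weight and leaves the primary endpoint unchanged.

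**What to change.** 1. Reconcile the window with the entry age: define baseline as the lowest stable creatinine before the current illness, including values from the 90 days before admission, and use older values only as fallback.
2. Flag each child's baseline as measured or assumed.
3. As a sensitivity analysis, report AKI incidence and RAI accuracy in children with a measured baseline beside the results for all children.
4. Rename the clearance item as percent change in creatinine, which is what is calculated.

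**Cost.** Items 2 to 4 need derivation code, a table and a label. Item 1 is dearer than a change of definition: the Discussion reports over 3,500 children already enrolled, about two thirds of the planned 5,250 (3,500/5,250 = 67%), and site staff are not paid for this study. Some sites would have to go back to the record and enter a creatinine already there. If that is not feasible, item 3 alone needs no new data. It would then describe only children with a value that meets the present window, who may differ from the rest, and the report should say so.

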### Analysis

Analysis of data will be performed independently based on each specific aim.Data for the primary objective of describing the epidemiology of AKI will be presented as a descriptive model. The prevalence on day 0 and incidence of AKI in up to 7 days of ICU admission using KDIGO classification will be calculated for each site cohort to identify the geographical “hot spots” of pediatric AKI. The data then will be pooled into a single cohort to study the outcome of AKI. The whole cohort will be stratified on Day 3 into four sub-populations with: no AKI, AKI-KDIGO Stage 1, AKI-KDIGO Stage 2, and AKI-KDIGO Stage 3. An adjusted and unadjusted survival analysis models using log rank test and cox regression models will be used to compare the mortality rates and the need of renal replacement therapy between the 4 groups.The prognostic value of the renal angina index will be calculated on Day 0 for the development of Day 3 AKI. RAI will be evaluated as a diagnostic test and sensitivity, specificity, positive predictive value, negative predictive value, likelihood ratios, and receiver operating characteristics (ROCs) will be derived.Individual prognostic values of each of the four urinary biomarkers al one for Day 3 AKI will be calculated. The biomarkers will be tested in combination for changes in prognostic parameters and comparisons of discrimination using net reclassification improvement (NRI) and integrated discrimination improvement (IDI) will be derived. Finally, the contribution of each biomarker to the predictive model of renal angina for Day 3 AKI will be analyzed by integrating the biomarkers alone and in combination with the RAI.

Additionally, the association of renal angina index, urinary biomarker levels with clinical outcomes, including mortality, PICU length of stay, hospital length of stay, and renal replacement therapy provision, will be assessed using Chi-square test (or Fisher’s exact test for small counts) or Pearson correlation coefficient (or non-parametric Spearman correlation coefficient) based on the nature of data. Classification and regression tree analysis will be used to determine optimal decision rules for biomarker incorporation with RAI when discriminating for Day 3 AKI. In all analyses, a p-value of <0.05 will be considered statistically significant.

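### The measured baseline creatinine has no outer look-back limit and no adjustment for body size, so growth or slow CKD decline can be staged as AKI

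*Protocol article*

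**What the plan says.** All references are to the protocol article.

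- **Variable collection**, on children with a prior measurement: "Baseline creatinine used is lowest consistent serum creatinine". The rest of the sentence sets only the near end of the window: "lowest consistent serum creatinine 90 days or more prior to admission". Daily change is the percent change in raw creatinine from this value. The word *consistent* is not defined.
- **Variable collection**, on children without one: "For patients without a prior baseline, an assumed creatinine clearance of 120 ml/min/1.73 m^2^ is used". This fallback is normalised to body size; the measured baseline is not.
- **Inclusion criteria**: age from 90 days to under 25 years.
- **Exclusion criteria**: besides maintenance dialysis and a recent kidney transplant, the renal exclusion is "Chronic kidney disease with a baseline estimated glomerular filtration rate (eGFR) of < 15 ml/min/1.73 m^2". Children with less advanced CKD are enrolled.
- **Primary and secondary outcomes**: "AKI is defined as KDIGO stage 2 or 3 AKI by creatinine and/or urine output criteria on Day 3 or later".
- **Analysis**: the cohort is split on Day 3 into "no AKI, AKI-KDIGO Stage 1, AKI-KDIGO Stage 2, and AKI-KDIGO Stage 3", so stage 1 counts as well.
- **Discussion**, on limitations: "Many pediatric patients have no ‘baseline’ creatinine measured prior to the time of acute illness". Only the missing baseline is discussed, not an old one.

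**The concern.** The window opens 90 days before admission and runs back without end. Choosing the lowest value in it favours old values. In a growing child these were taken at a smaller body size, and in a child with progressive CKD they were taken before the decline. Neither growth nor slow decline is acute injury, yet both raise the ratio of today's creatinine to the baseline.

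If KDIGO staging uses this baseline, the error enters the creatinine part of Day 3 AKI, the site-level incidence used to look for geographical hot spots, the four Day 3 survival groups, and the target against which the renal angina index (RAI) and the biomarkers are judged. It works in one direction and is tied to age, chronic illness and depth of past records, so a larger sample will not average it out. The abstract says the RAI uses early change in creatinine. If it shares the baseline, predictor and outcome share the error and their agreement is overstated. The RAI's own definition is in an additional file that is not shown, so this last step is conditional.

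**Working it through.** The plan gives no figure that depends on the baseline rule. Its sample size (150 × 35 = 5,250) reproduces and is unaffected. The check is therefore the ratio of admission creatinine to baseline creatinine in a child with no acute injury.

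**Assumptions, not printed in the article:** creatinine is proportional to height at constant size-normalised clearance; stages 1, 2 and 3 start at 1.5, 2 and 3 times baseline; the heights and eGFR values are illustrative.

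**Growth.** With creatinine = k × height / clearance and clearance constant, the ratio is height now / height at baseline.

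| Baseline height (cm) | Height now (cm) | Ratio | Stage without injury |
|---|---|---|---|
| 60 | 75 | 1.25 | none |
| 75 | 110 | 1.47 | none |
| 75 | 120 | 1.60 | 1 |
| 87 | 170 | 1.95 | 1 |
| 60 | 120 | 2.00 | 2 |
| 75 | 170 | 2.27 | 2 |

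**Growth plus a mild true rise.** The acute rise needed to reach 2 times baseline is 2 / growth ratio. After growth from 75 to 120 cm this is 2 / 1.60 = 1.25. A rise that would not reach the assumed stage 1 ratio is then read as stage 2.

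**Chronic decline at constant size.** The ratio is eGFR at baseline / eGFR now.

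| eGFR at baseline | eGFR now | Ratio | Stage without acute injury |
|---|---|---|---|
| 120 | 90 | 1.33 | none |
| 120 | 80 | 1.50 | 1 |
| 60 | 30 | 2.00 | 2 |
| 30 | 15 | 2.00 | 2 |
| 90 | 30 | 3.00 | 3 |

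Every row ends at 15 or above, so none meets the eGFR exclusion.

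**The two baseline rules side by side.** Take two healthy patients of 170 cm, each with a clearance of 120. The one with no record is given a baseline back-calculated from 120, so the ratio is 1.0. The one whose lowest prior value dates from 75 cm has a ratio of 170 / 75 = 2.27. The same patient is unaffected under one rule and stage 2 under the other.

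**Scale of the effect on incidence.** If a fraction f of children without severe AKI is wrongly staged as severe, the observed incidence is p + (1 − p) × f. For f from 1% to 10% (assumed), a true 10% (assumed) reads 10.9% to 19.0%. A true 18% (the figure the article cites from a large adult study) reads 18.8% to 26.2%. The article gives nothing from which to estimate f, so this shows sensitivity only.

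**The case against.** Several points on the other side have force.

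- **Age of the value, not the minimum, does most of the damage.** A child whose only record is an old one has the same error under a most-recent rule, and a short look-back largely removes the growth error even if the lowest value is kept (60 to 75 cm gives only 1.25). This stands, and it is why the fix targets the window. A reader might infer that the lowest value must be the earliest one, or that taking the lowest of many tests inflates the ratio materially by itself. The documents do not support either: the rule asks for a consistent value, which may screen out isolated lows, and no within-child variation is given.
- **Growth seldom reaches the primary outcome alone.** Creatinine must about double. A reader might infer that older children in general are counted as severe AKI; the table shows otherwise. This stands for growth. Chronic decline reaches stage 2–3 more readily.
- **Staging on this baseline is inferred.** The KDIGO stage is listed as a separate item that refers only to the guideline. The inference is natural, since no other baseline is printed, but it is an inference.
- **An article condenses.** A look-back limit could be in the full protocol or the case report forms, and this cannot be excluded. But the article does state the rule, with an inner limit and no outer one.
- **A recent value has its own bias.** Children tested often may have been ill recently, so a recent value may be raised and hide true AKI. This stands, and is one reason to keep the present rule as a sensitivity analysis.

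**Conclusion.** The concern holds in a limited form. Applied as printed, the measured-baseline rule can label growth or slow CKD decline as AKI in eligible patients, and nothing in the article counters this. Under the stated assumptions the ratio without injury is 1.60 for growth from 75 to 120 cm, 2.27 from 75 to 170 cm, 2.0 for an eGFR fall from 60 to 30, and 3.0 from 90 to 30. Growth alone enters the stage 2–3 outcome only when an infant or toddler value is used years later. More often it creates a false stage 1 or lifts a mild true rise into stage 2.

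The number of children affected cannot be worked out from the article. Children without a prior value are untouched, as is staging by urine output. The conclusion rests on proportionality of creatinine to height, on the assumed cut-offs, and on KDIGO staging using the printed baseline.

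**What to change.** 1. Bound the look-back to a recent pre-illness window, for example the last year, and use a stable value or the median within it. Say how stability is judged.
2. Where only older values exist, use the plan's own fallback of 120 ml/min/1.73 m², back-calculated at admission height. For known CKD, use the most recent stable value.
3. State that KDIGO staging uses this baseline, and whether the RAI does.
4. Record the date of the baseline value.
5. Keep the lowest value at any time as a sensitivity analysis, and report how many children change KDIGO stage.

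**Cost.** One definition changes and one date field is added. Historical heights are not needed, because the fallback works at admission height and the plan already needs that calculation for children with no prior value. The Sample size section allows data capture after each site's enrolment period. The date must still be retrieved for children already enrolled (over 3,500 at the time of writing, per the Discussion), at sites that are not paid for the work. Some recent values may reflect unresolved injury, and some growth or decline within the window will remain.
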